## Abstract

**Background:**

The prevalence of obesity is escalating alarmingly worldwide, and it is now becoming a rapidly growing epidemic in developing countries. Recent studies have reported that zinc has been implicated in altered lipid markers, insulin resistance and some obesity markers. There is a lack of evidence on zinc as a potential therapeutic agent to reduce weight and improve metabolic parameters in obese adults. The present study is designed to evaluate the effects of zinc supplementation on obese adults in Sri Lanka. Furthermore, we aim to evaluate the effects of zinc supplementation on metabolic parameters in this population.

**Methods/design:**

This study will be conducted as a randomized, double-blind, placebo-controlled clinical trial for a period of 3 months at the clinical laboratory, Department of Applied Nutrition, Wayamba University of Sri Lanka to assess the efficacy of daily zinc 20 mg supplementation in obese subjects. There will be a total of 80 subjects, aged between 18–60 years, of both genders, who are obese (body mass index (BMI) ≥25). Subjects will be stratified according to age, gender and BMI and randomly assigned into the test and placebo groups in a 1:1 ratio. The treatment drug is a capsule containing elemental zinc 20 mg as the active ingredient (as zinc sulphate). The placebo capsule will contain lactose monohydrate. The subjects will receive either zinc capsules or placebo daily for 3 months. The study treatments will be double blinded to both investigator and subject. The visits and the evaluations will be as follows: screening (visit 0), baseline (visit 1) and 3 month (visit 2). The primary outcome will be weight reduction among the obese subjects. Secondary outcome measures include glycaemic status (fasting blood glucose), lipid parameters (total cholesterol, triglyceride levels, high-density lipoprotein cholesterol, low-density lipoprotein cholesterol) and blood pressure.

**Discussion:**

The trial protocol will aim to establish the effects of zinc supplementation on weight reduction and metabolic risk parameters among obese subjects.

**Trial registration:**

Sri Lanka Clinical Trials Registry: SLCTR/2014/020. Registered on 18 September 2014.

## Background

The prevalence of obesity is escalating alarmingly worldwide, and now it is becoming a rapidly growing epidemic in developing countries including south Asia [1]. Obesity is a major public health problem in Sri Lanka [2]. The level of obesity in Sri Lanka has increased several fold during last two decades, and nearly a quarter of adults have a body mass index (BMI) of more than 25 [3]. More seriously, obesity-associated metabolic problems such as diabetes (~11 %) [4], hypertension (~20 %) [4] and metabolic syndrome (~25 %) [5] are also highly prevalent among Sri Lankan adults. On the other hand, several micronutrient deficiencies are also still major public health issues in Sri Lanka, including zinc deficiency [6].

A low plasma zinc level is associated with obesity [7, 8]. Zinc may regulate serum leptin concentration [9] and appetite control. Zinc (Zn), an essential micronutrient and a component of many enzymes, is involved in the synthesis, storage and release of insulin [10]. Studies have reported that Zn has been implicated in altered lipid markers, insulin resistance, oxidative stress, inflammatory markers [11, 12], adiposity and serum leptin level [13]. Furthermore, a recent review and meta-analysis reported that zinc supplementation has favourable effects on plasma lipid parameters and that it also significantly reduces total cholesterol, low-density lipoprotein (LDL) cholesterol and triglycerides [14]. A high prevalence of coronary artery disease (hypertension, hypertriglyceridaemia and low high-density lipoprotein (HDL) cholesterol levels), diabetes and glucose intolerance was reported in populations consuming lower intakes of dietary zinc [15]. Although there is accumulating evidence on the relationship between serum zinc and human metabolism, there is a lack of evidence on Zn as a potential therapeutic agent to reduce weight and improve metabolic parameters in obese adults. Thus, this study aims to evaluate the effects of Zn supplementation on weight reduction and metabolic parameters in obese adults in Sri Lanka.

## Methods/design

### Study design

This is a randomized double-blind, placebo-controlled clinical trial.

### Setting

The proposed clinical trial will be held at the clinical laboratory, Department of Applied Nutrition, Wayamba University of Sri Lanka for 3 months to assess the efficacy of daily zinc 20 mg supplementation in obese subjects. Figure 1 illustrates the timeline of the study.

**Fig. 1 Fig1:**
[figure not shown]
Timeline of the study

### Participants (inclusion and exclusion criteria)

Subjects will be obese (BMI ≥25) individuals aged between 18–60 years of both genders. Definitions for anthropometric cut-offs for obesity were based on WHO cut-offs for Asians [16]. The following exclusion criteria will be applied: subjects on any other vitamin or mineral supplementations or the current use of a weight loss medicine or special dietary modification, history of diabetes mellitus or any metabolic disease, alcohol consumption >20 g/day, presently having acute diseases or other untreated illness requiring treatment, impaired hepatic or renal functions, lactation, pregnancy or unwillingness to use an effective form of birth control for women of child-bearing years and history or presence of any condition, in the investigator’s opinion, that would endanger the individual’s safety or affect the study result. Furthermore, subjects will be suspended from the study if they demand to discontinue it and/or have low rates of compliance.

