### Randomization and blinding

After the screening phase, subjects will be stratified according to age, gender and BMI and randomly assigned to one of two groups of 40 subjects each into the test and placebo. Assignment to either group will be performed by a computer-generated 1:1 randomization. The study treatments are double blinded to both investigator and subject. The supplements and placebo will be produced by Astron Lanka Limited, Ratmalana, Sri Lanka. They will be responsible for the labelling and packaging of the Zn capsule and placebo with code numbers.

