### Interventions

The study will be conducted for 3 months. The visits and the evaluations will be as follows: screening (visit 0), baseline (visit 1) and 3 month (visit 2). The treatment drug is a capsule containing elemental zinc 20 mg as the active ingredient (as zinc sulphate). The supplemented Zn dose was set based on a previous study published in the literature [14]. The placebo capsule will contain lactose monohydrate. The placebo will be manufactured to have a similar appearance, shape, weight, taste and colour as the Zn capsule. The subjects will receive either one capsule of Zn or an identical placebo daily, taken after dinner for a period of 3 months. Figure 1 illustrates the schedule of the study.

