### Sample size

The minimum estimated sample size was 35 for each study arm, and a 15 % dropout rate was calculated. Finally, 40 subjects were recruited for each group.

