### Compliance calculation

Subjects are asked to return any remaining drugs, and their compliance will be evaluated by using the formula:$$ \mathrm{Compliance}\left(\%\right)=\frac{\mathrm{Distributed}\ \mathrm{capsules}\hbox{-} \mathrm{remainining}\ \mathrm{capsules}}{\mathrm{Distributed}\ \mathrm{capsules}}\times 100 $$

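### Suspending randomised subjects from the study for low compliance can lose or exclude their 3-month weight, so the comparison may no longer be of the groups as randomised

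*Protocol article*

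**What the plan says.** The rule closes the list of exclusion criteria in the protocol article, section Participants (inclusion and exclusion criteria): "subjects will be suspended from the study if they demand to discontinue it and/or have low rates of compliance". The object is the study, not the capsules.

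Three other sections determine when it can operate:

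- Randomization and blinding describes the order of events: "After the screening phase, subjects will be stratified according to age, gender and BMI and randomly assigned to one of two groups of 40 subjects". Allocation therefore precedes any dosing.
- Compliance calculation: "Subjects are asked to return any remaining drugs, and their compliance will be evaluated by using the formula", which is capsules distributed minus capsules remaining, over capsules distributed, times 100. No value is given below which compliance counts as low.
- Interventions: the visits are "screening (visit 0), baseline (visit 1) and 3 month (visit 2" (the 3-month visit is the last in the list).

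Statistical analysis names a t test or Wilcoxon test between the two groups and regression models. It does not say which subjects enter them. No section says that suspended subjects are still measured at visit 2 or kept in the analysis.

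**The concern.** Although it sits among the eligibility criteria, the low-compliance rule is not an eligibility criterion. Compliance does not exist until capsules have been dispensed and returned, so the rule selects on something that happens after randomisation. Such behaviour can be influenced by the treatment, through tolerability, and by the outcome, because a subject whose weight is not falling may stop taking capsules. Randomisation makes the two arms comparable at entry. It does not make the compliers of one arm comparable with the compliers of the other.

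What is at stake is the primary comparison of weight reduction. If those removed differ between arms, the estimate mixes the effect of zinc with the effect of selection, yet it would be reported with the authority of a randomised double-blind trial. Where suspension comes before the 3-month visit, the missing weights cannot be recovered by any later choice of analysis.

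**Working it through.** **1. When the rule can act.** Randomisation follows screening and compliance is counted from returned capsules, so removal for low compliance is always after randomisation. With one listed post-baseline visit there are two cases:

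| Suspension | Weight at 3 months | Consequence |
|---|---|---|
| Before visit 2 | Not obtained if the subject is out of the study | Missing primary outcome, related to compliance |
| At visit 2 | Can be measured | Measured subject may be left out, on a threshold not fixed in the article |

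The article does not say when capsules are counted or who judges compliance, and the timeline figure is not shown. Neither case can be ruled out.

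**2. The plan's own figure.** Sample size states: "The minimum estimated sample size was 35 for each study arm, and a 15 % dropout rate was calculated", giving 40 per arm.

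- Dividing by the retained fraction: 35 / (1 − 0.15) = 41.2.
- Multiplying up: 35 × 1.15 = 40.25.

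Both are close to 40, and this point does not depend on the difference. The 35 itself cannot be reproduced, because no effect size, SD or power is given.

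**3. Possible size of the bias (illustration).** From the documents: 40 per arm, 1:1 allocation, significance level 0.05. Assumed, because the documents give no values: two-sided test, no true effect, SD of weight change 3 kg, removed subjects on average 2 kg worse than their arm mean, normal approximation.

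If a fraction p is removed and those subjects lie 2 kg on the unfavourable side of an arm mean of 0, the retained mean shifts by p × 2 / (1 − p) in the favourable direction. The bias is the difference between the two shifts. The standard error is 3 × √(1/n₁ + 1/n₂), with n = 40(1 − p). With k = bias / SE, type I error is Φ(−1.96 + k) + Φ(−1.96 − k).

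| Removed, zinc v placebo | Shift, zinc (kg) | Shift, placebo (kg) | Bias (kg) | n retained | SE (kg) | Type I error |
|---|---|---|---|---|---|---|
| 15% v 15% | 0.353 | 0.353 | 0 | 34, 34 | 0.728 | 5.0% |
| 15% v 5% | 0.353 | 0.105 | 0.248 | 34, 38 | 0.708 | 6.4% |
| 20% v 5% | 0.500 | 0.105 | 0.395 | 32, 38 | 0.720 | 8.5% |

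The biases in the last two rows favour zinc. Exchanging the arms gives the same sizes in favour of placebo.

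**4. A wider range in SD units.** Let removed subjects differ from *retained* subjects by m SD in both arms. The bias is then (p₁ − p₂) × m.

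| Removed | m = 0.25 | m = 0.5 | m = 1.0 |
|---|---|---|---|
| 15% v 15% | 0; 5.0% | 0; 5.0% | 0; 5.0% |
| 15% v 5% | 0.025 SD; 5.1% | 0.05 SD; 5.5% | 0.10 SD; 7.1% |
| 25% v 5% | 0.05 SD; 5.5% | 0.10 SD; 6.9% | 0.20 SD; 13.0% |

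Equal rates give zero bias here only because the removed subjects are taken to be of the same kind in both arms. If the kind differs, equal rates do not protect.

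**The case against.** The strongest reply is that one sentence is being made to carry too much. Several parts of that reply stand.

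- **Outcome-aware exclusion.** A reader might infer that compliance is judged at visit 2, with final weight in hand. The article does not say so. With the timeline figure not shown, earlier capsule counts are possible, and then the problem is missing data instead.
- **A per-protocol analysis.** A reader might infer that the primary analysis is of compliers only. No analysis set is named, and that is commonly left to the full protocol or analysis plan. Being suspended from the study is not literally the same as being excluded from the analysis. Nor is the absence of a numerical cut-off in the article a fault in itself.
- **Discontinuation.** Any subject may leave a trial, so the part about those who ask to discontinue may describe ordinary withdrawal.
- **Sample size.** A reader might infer that suspensions cut the sample beyond the planned loss. The article says only that "a 15 % dropout rate was calculated" and does not define dropout, so the allowance may already include them.
- **Size and direction.** The article expects high compliance, reports no known adverse effects at 20 mg/d, and describes a matched placebo with investigator and subject blinded. These make strongly unequal removal less likely, and nothing in the document says which arm would lose more.

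What does not stand is that the rule is therefore harmless. It is a stated rule, not an omission. Blinding limits knowing selection by arm but not selection through tolerability or a perceived lack of effect. An analysis plan that specifies analysis as randomised cannot supply weights that were never measured. If compliance is as high as expected, the rule gains little.

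**Conclusion.** The point holds for the low-compliance limb. The article states a rule that takes randomised subjects out of the study on a post-randomisation measure, and nothing in it keeps them in follow-up or in the analysis. The comparison of weight reduction may then not be of the groups as randomised, whether through missing 3-month weights or through leaving out measured subjects.

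The size of the bias cannot be fixed from the document. It is zero if equal fractions of similar subjects are removed. Under the assumed SD of 3 kg and 2 kg deficit it is about 0.25 to 0.40 kg, with type I error of 6.4% to 8.5%, for removal of 15% or 20% in one arm against 5% in the other; the direction follows the arm that loses more. These figures show what the rule could do, not what it will do.

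For the discontinuation limb only a narrower point holds: the text does not separate stopping capsules from withdrawing from follow-up.

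**What to change.** - Delete removal from the study for low compliance.
- State that every randomised subject is asked to attend visit 2 for weight and the secondary measurements, whatever the capsule count, unless consent to follow-up is withdrawn.
- For subjects who ask to discontinue, record separately whether they are stopping capsules or withdrawing from follow-up, and seek visit 2 measurements from the former.
- Make the primary analysis one of all randomised subjects in their assigned group.
- If a compliers analysis is wanted, label it supportive and fix its cut-off before unblinding.

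The cost is a change of protocol wording and a few more attendances at a visit that is already scheduled. The estimate may be slightly diluted by non-adherence. Trial status reports that the trial is still recruiting, so on that account the change can still preserve outcomes that would otherwise be lost.

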### Randomization and blinding

After the screening phase, subjects will be stratified according to age, gender and BMI and randomly assigned to one of two groups of 40 subjects each into the test and placebo. Assignment to either group will be performed by a computer-generated 1:1 randomization. The study treatments are double blinded to both investigator and subject. The supplements and placebo will be produced by Astron Lanka Limited, Ratmalana, Sri Lanka. They will be responsible for the labelling and packaging of the Zn capsule and placebo with code numbers.

### Interventions

The study will be conducted for 3 months. The visits and the evaluations will be as follows: screening (visit 0), baseline (visit 1) and 3 month (visit 2). The treatment drug is a capsule containing elemental zinc 20 mg as the active ingredient (as zinc sulphate). The supplemented Zn dose was set based on a previous study published in the literature [14]. The placebo capsule will contain lactose monohydrate. The placebo will be manufactured to have a similar appearance, shape, weight, taste and colour as the Zn capsule. The subjects will receive either one capsule of Zn or an identical placebo daily, taken after dinner for a period of 3 months. Figure 1 illustrates the schedule of the study.

### Measurements

The primary endpoint is weight reduction among obese adults. Body weight will be measured using a calibrated electronic floor scale (SECA 815 by SECA GmbH & Co. KG, Hamburg, Germany) to the nearest 0.1 kg. Height will be measured to the nearest 0.1 cm using an upright plastic portable stadiometer (IP0955, Invicta Plastics, Leicester, UK). BMI will be calculated as weight (in kilograms) divided by the square of height (in metres). Waist circumference will be measured with a non-elastic tape (SECA 203 by SECA GmbH & Co. KG, Hamburg, Germany) at a point midway between the lower border of the rib cage and the iliac crest at the end of normal expiration. Similarly, the hip circumference also will be measured at the widest part of the buttocks at the intertrochanteric level to the nearest 0.1 cm. All anthropometric measures will be taken by trained research assistants using standard equipment according to the standard guidelines [17]. In addition, glycaemic status (fasting blood glucose), lipid parameters (total cholesterol, triglyceride levels, HDL cholesterol, LDL cholesterol) and blood pressure will be measured. Glucose in the plasma will be determined by the glucose oxidase/peroxidase (GOD-Perid) method using commercially available kits (ProDia International, USA) and a chemistry analyser (Erba Chem-7, UK). Total cholesterol, triglyceride levels and HDL cholesterol (HDL-C) will be measured with enzymatic colorimetric assays using commercially available kits (ProDia International, USA) and an Erba Chem-7 chemistry analyser (Erba Molecular, Cambridgeshire, UK). LDL cholesterol (LDL C) will be estimated based on the Friedewald equation [18]. Systolic (SBP) and diastolic blood pressure (DBP) will be measured after at least a 10-min rest with Omron IA2 digital blood pressure monitors (Omron Healthcare, Singapore).

### Sample size

The minimum estimated sample size was 35 for each study arm, and a 15 % dropout rate was calculated. Finally, 40 subjects were recruited for each group.

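### Forty per arm does not quite cover the stated 15% dropout: 34 are expected to remain, one below the declared minimum of 35

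*Protocol article*

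**What the plan says.** The protocol article's Sample size section consists of three figures. The first is the target: "The minimum estimated sample size was 35 for each study arm". The second is a 15% allowance for loss, and the third is the resulting size: "dropout rate was calculated. Finally, 40 subjects were recruited for each group".

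The 40 is confirmed elsewhere. Randomization and blinding has subjects "randomly assigned to one of two groups of 40 subjects each" and fixes the ratio: "Assignment to either group will be performed by a computer-generated 1:1 randomization". The Methods/design part of the abstract gives the total: "There will be a total of 80 subjects". So 40 per arm and 80 overall are the intended figures, not a misprint.

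The article does not say how the 15% was applied to the 35. It also gives no effect size, SD or power behind the 35.

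**The concern.** A dropout rate is normally the share of enrolled subjects who are lost. A size that allows for it should leave at least the required number once that share is gone. On that reading the three printed figures do not agree, because 40 per arm falls one short of 35 after 15% loss.

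This is a relation between figures that the article itself prints, so neither the condensed format nor a separate analysis plan could resolve it. It matters because these figures are all the sample-size justification a reader of the article has. At stake is whether the trial, under its own dropout assumption, keeps the number it calls its minimum, and so whatever power that minimum was meant to give.

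**Working it through.** **Inputs.** From Sample size: minimum 35 per arm, dropout 15%, recruited 40 per arm. From Randomization and blinding: 40 per arm, 1:1. From the abstract: 80 in total.

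**1. Reproducing the 40.** Adding 15% to the minimum: 35 × 1.15 = 40.25. Rounded to the nearest whole number this is 40, the stated figure. Rounded up, as is usual for a required minimum, it is 41. The article does not state this route, but it is the likely one.

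**2. What 40 leaves.** 40 × (1 − 0.15) = 34.0 per arm, or 80 × 0.85 = 68 in total, against 35 per arm and 70 in total.

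**3. What 35 needs.** 35 / (1 − 0.15) = 41.18, so 42 per arm and 84 in total. Check: 42 × 0.85 = 35.7.

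**4. What 40 can absorb.** 1 − 35/40 = 0.125. Forty per arm keeps 35 for losses up to 12.5%, that is, 5 subjects per arm.

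**5. Cost in power (illustration).** The article gives no power, so I assume that 35 per arm was chosen for 80% or 90% power in a two-sided 5% two-sample t test, and use the noncentral t distribution.

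| Assumed power at 35 per arm | Implied standardised difference | Power at 34 per arm |
|---|---|---|
| 80% | 0.679 | 78.8% |
| 90% | 0.786 | 89.1% |

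The loss is about one percentage point in either case. Put the other way, the difference detectable with 80% power moves from 0.68 SD at 35 per arm to 0.69 SD at 34.

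**6. Chance of ending below 35.** Assume that each subject drops out independently with probability 0.15. An arm falls short if 34 or fewer remain.

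| Recruited per arm | One given arm below 35 | At least one arm below 35 |
|---|---|---|
| 40 | 0.567 | 1 − (1 − 0.567)² = 0.81 |
| 42 | 0.289 | 1 − (1 − 0.289)² = 0.50 |

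Inflating for expected dropout protects the minimum only on average. Even at 42 per arm, the chance that at least one arm falls short is about one half.

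**The case against.** The best defence is that the 40 has an evident origin. Adding 15% to 35 and rounding to the nearest whole number gives 40, and the result is within two subjects per arm of the correct inflation. That stands as an explanation. A reader might infer that the three figures cannot be reconciled by any method or rounding rule; the 40.25 shows otherwise. But explaining the figure does not make it sufficient. The shortcut applies 15% to the number to be kept instead of the number enrolled, and rounding down a required minimum adds to the gap.

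Two other stronger readings also go further than the article allows:

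- A reader might take the 81% chance that at least one arm ends below 35 as the effect of the error. It is not, since the same chance is about 50% with 42 per arm. Much of the 81% is ordinary chance variation in dropout.
- A reader might infer that removing subjects with low compliance, as the Participants section provides, thins the numbers further. That section names withdrawals and low compliers together, and nothing says that the 15% excludes the latter. They may already be counted in it. The article also says, under Strengths and weaknesses, that it expects high compliance.

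It can also be said that the article calls 35 an estimated minimum sample size and never says that it means subjects remaining at the end. That is correct. Still, a dropout allowance placed on top of a minimum has little purpose on any other reading.

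**Conclusion.** The sentence is wrong as written, and the error is minor. With 40 per arm and 15% dropout, 34 per arm are expected, one below the declared minimum; the allowance that 40 actually provides is 12.5%. This part is plain arithmetic on printed figures and rests on one inference, that 35 is the number meant to remain after dropout.

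The cost of about one percentage point of power rests on an assumed 80% or 90% design power and a two-sided 5% t test, because the article states no design inputs. It would be wrong to infer that the design fails or that the trial's conclusions are at risk. Endpoint, allocation and analysis are unaffected.

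**What to change.** Keep 80 subjects and correct the statement in Sample size, for example: *40 per arm allows for 12.5% dropout and leaves 35 per arm; at 15% dropout, 34 per arm are expected.*

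This costs one sentence and no extra subjects. The downside is that the stated dropout tolerance becomes slightly less favourable.

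If the sponsor prefers to keep the 15% allowance, the consistent size is 42 per arm. That is four more subjects in total, and the 40 and 80 given in the abstract and under Randomization and blinding would have to change with it. The Trial status section says that the trial is still recruiting, so this may be possible, but a gain of about one point of power does not require it.
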